### Treatments

#### Overview

Both CBT conditions include 10 treatment modules delivered over 10 consecutive weeks. Treatments are delivered by either a PhD-level psychologist or the study nurse trained and supervised by a clinical psychologist with specific competencies and experience in delivering CBT for chronic pain. Therapists follow treatment manuals and participants are provided with a treatment-specific participant handbook. The 10-week course of therapy consists of an introductory module, followed by 8 consecutive pain coping skills modules, and concludes with a 10th module emphasizing skill consolidation and relapse prevention. Both conditions include the same pain coping skills, which were selected from a wider collection of possible skills because they were rated most highly by participants in a prior funded trial on importance, interest and ability to engage in them [21] (see Table 1 for description of skills). Participants assigned to both conditions continue to receive routine care of their CLBP by their current healthcare providers. Study staff do not attempt to influence clinical care other than CBT in any way.

*CBT* involves weekly, 30-minute, individual in-person sessions with a therapist, a pedometer-facilitated walking program and daily IVR assessment. Each session includes one treatment module.

Each module includes: (1) the presentation of an explicit rationale for development and use of the specific coping skill being taught, (2) a description of each coping skill, skill modeling and practice of the skill during the session, (3) problem-solving about the practice and use of the specific skill, and (4) assignment of a specific goal for practice of the week’s skill and collaboration between the therapist and participants to develop a weekly goal for engaging in pleasant or meaningful activities.

*IVR-CBT* is an adapted form of in-person CBT specifically designed for the IVR environment. IVR-CBT involves reading handbook materials, a pedometer-facilitated walking program, daily IVR assessment and retrieval of pre-recorded therapist feedback related to treatment engagement and goal completion. Participants in the IVR-CBT condition have access to extra IVR features not available to participants in the in-person CBT condition. For example, optional pre-recorded, brief audio segments are provided to reinforce the information about pain coping skills that are presented in the patient handbook and offer participants with poor literacy skills an additional opportunity to learn the treatment skills. Peer testimonials feature a voice actor speaking the words of an actual participant in one of our prior trials of CBT for chronic pain describing their successful use of the pain coping skills. A collection of short motivational tips also are available.

#### IVR-CBT therapist feedback

Each week the therapist reviews participants’ IVR-reported data via a web interface that summarizes the daily reports (see Fig. 2). Therapists comment on participants’ average pain intensity, sleep, steps, and skill practice for the week and note the weekly average, any change from the prior week, either positive or negative, and note any patterns (e.g., more pain on weekends versus week days). Therapists also provide reinforcement for any goal accomplishment and note potential associations among pain, goal accomplishment, and pain coping skill practice. Therapists provide corrective feedback on any incorrect answers to the true/false questions. Finally, therapists assign a steps goal for the upcoming week.

**Fig. 2 Fig2:**
[figure not shown]
Screen shots of study dashboard views

#### Treatment fidelity measures

In-person CBT and IVR-CBT Treatment Receipt/Comprehension: The measures of treatment receipt (i.e., the five- item true/false content questionnaire) have been described above. We will analyze and report these data regarding average level of skill comprehension and whether any treatment modules were more difficult for participants to understand. Treatment fidelity will be assessed by psychologists with expertise in CBT for chronic pain, who will rate audiotapes of 30 % of the in-person CBT sessions and the IVR-CBT weekly feedback recordings to assure that key components of the manuals are covered. Percentages of treatment integrity/violations will be calculated. The study’s psychologist principal investigator will provide corrective feedback to the psychologist whenever drift occurs.

#### Adverse events

Although walking is not considered risky for patients with chronic musculoskeletal pain and is often recommended, information about adverse events associated with participation in the walking portion of the treatment is solicited once per week during the IVR assessment calls. Participants may report adverse events by recording a brief audio message. These messages are reviewed each business day by study staff and any reports that indicate a cause for concern are followed-up with the participant, their primary care provider, or both.

#### Outcomes

Survey outcomes are assessed at 4 time points, baseline, post-treatment, and 6 and 9 months post baseline. Participants are given up to 14 weeks to complete treatment in order to accommodate rescheduled sessions due to vacations, illness or travel difficulties. Post-treatment data are collected when a participant completes treatment or at 15 weeks post-baseline regardless of whether the participant has completed treatment. Survey outcomes are assessed using the TrialDB system, which allows participants to complete the self-report questionnaires online via a secure web-based interface. Participants who do not have an Internet connection may come to the medical center to complete the measures via TrialDB or complete a paper version of the measures and return them by mail. IVR outcomes will be assessed daily during the baseline week and over the 10 treatment weeks.

Measures were selected based on the Initiative on Methods, Measurement and Pain Assessment in Clinical Trials (IMMPACT) recommendations [23], which called for the assessment of multiple domains of the pain experience in all pain treatment trials and recommended measures based on their psychometric properties and respondent burden. These measures are consistent with CONSORT guidelines for non-inferiority trials [24] that recommend that outcome measures be similar to those used in studies to establish efficacy of the reference treatment.

*Primary Outcome - Pain intensity:* We assess participants’ average pain intensity over the past week via survey, at the four outcome assessment points using the Numeric Rating Scale of pain intensity (NRS-I) [25] an 11-point numeric rating scale (0 = no pain, 10 = worst pain imaginable). The primary outcome is the average weekly pain intensity at post-treatment.

*Secondary Outcomes – Pain intensity* will also be assessed daily during the trial via the IVR system using the NRS scale. Subjects will have a maximum of 77 daily scores: 7 daily calls for the baseline assessment week and 7 daily calls for each of the 10 weeks of treatment. We will use these scores to compute weekly means for each subject. The mean of seven daily assessments has been found to provide reliability in excess of 0.90 [26].

*Physical functioning:* The nine-item Interference subscale of the West Haven-Yale Multidimensional Pain Inventory (WHYMPI) is used to assess pain-related interference in social, work and household activities and has demonstrated good internal consistency (.86) and stability (.85 over 2 weeks) [27]. The 24 item Roland and Morris Disability Questionnaire is designed to assess physical functioning in patients with low back pain [28]. It has demonstrated good internal consistency (.84-.93) and stability (.83 over 3 weeks) [29].

*Emotional functioning:* Overall emotional functioning is assessed using the 65-item Profile of Mood States (POMS) [30], a multidimensional measure of emotional functioning designed to assess six dimensions of mood and to be used in non-psychiatric or physically ill populations. Internal consistency (0.84 to 0.95, depending on subscale) and test-retest reliability (0.65 to 0.74, depending on subscale) is good. Depression symptom severity is assessed using the 21-item Beck Depression Inventory-II [31] (BDI-II) a widely used self-report measure with excellent internal consistency (.94) and evidence of convergent and discriminant validity in primary care medical patients (.73–.96) [20].

*Quality of Life*: The Veterans SF-36 is used to assess health-related quality of life. This measure has demonstrated good internal consistency (.78–.93 across 8 subscales) and is strongly correlated with socioeconomic status and morbidities [32].

### Tertiary outcomes

*Adherence to coping skill practice* is assessed via IVR. Participants rate their daily practice of each week’s skills on a 0 (not at all accomplished) to 10 (completely accomplished) scale for each of the specified goals.

#### IVR call adherence

Call adherence is calculated as the total number of IVR calls made divided by the total number of expected calls (77).

#### Patient satisfaction

Patient satisfaction is assessed by a modified version of the Client Satisfaction Questionnaire-8 [33], an 8-item satisfaction survey designed to assess global satisfaction with treatment. This measure has been used widely to assess treatment satisfaction across numerous types of interventions and demonstrates good internal consistency (α = 0.87–0.93 across three samples) and has shown correlation to treatment attendance and retention.

#### Treatment attendance and drop out

Session attendance is tracked and the number of participants who do not complete follow-up assessments is calculated. In order to understand reasons for treatment dropout and evaluate “missingness” we prospectively collect data regarding reasons for treatment dropout and missing data. The research assistant, who monitors IVR and questionnaire completion, collects these data.

#### Sample size calculation

The sample size was calculated based on a test of non-inferiority comparing IVR-CBT to CBT, with 80 % power, Type I error (one-sided) of 0.025, and assuming the true difference between means is 0. Based on preliminary data from similar participants in an ongoing study of the efficacy of CBT for chronic back pain [21], the estimated baseline NRS pain intensity score will be 7 ± 2.45 units. A 20 % reduction in the NRS pain score from baseline to post-treatment, that is, from 7 to 5.6 or 1.4 units, is considered to be clinically relevant. The non-inferiority margin was set at one NRS unit, so that if the mean pain rating for IVR-CBT is less than one unit higher than the mean in-person CBT score (mean IVR-CBT < mean in-person CBT + 1), IVR-CBT will be deemed non-inferior. Conducting a test of this hypothesis can be done by comparing the upper limit of the 95 % confidence interval for the mean pain difference between IVR-CBT and in-person CBT with the non-inferiority margin 1; if this upper limit falls below 1, we will be able to conclude IVR-CBT is non-inferior. Based on these assumptions and 15 % inflation for losses, the total required sample size is 230 participants (115 per group).

### Analysis plan

#### Baseline analysis

The adequacy of the randomization will be assessed by comparing baseline demographic and clinical characteristics between the two treatment groups. Additional covariates will include number and location of pain sites and difference in medication use at baseline in order to assess whether these variables are associated with a differential response to the treatment.

#### Analysis

We present below the analysis of primary and secondary outcome measures only. Analysis of primary and secondary outcomes will employ linear mixed-effects models for longitudinal data, which will account for the clustering induced by repeated measures on individual patients. Mixed effects models make use of all available measurements on subjects and provide valid inferences even in the presence of missing data as long as the missingness is at random. Data from different subjects are assumed to be independent, while the correlation structure of the repeated measurements within subjects is modeled via parameterization of the covariance structure.

Between-group comparisons of the effectiveness of IVR-CBT and in-person CBT at each assessment time point will be conducted. Each of these comparisons can be tested separately within the same mixed-effect model using a treatment dummy variable, time dummy variables, and treatment-by-time interaction terms and appropriate contrasts. The outcome variable in each model will be the outcome at the follow-up time points, with the baseline value of the outcome and the stratification variables included as covariates in the model. Results will be summarized as LS- means (and their 95 % confidence intervals) within and between treatment groups at each time point. Non-inferiority will be demonstrated by the upper limit of the 95 % confidence interval for the LS-mean pain difference between IVR-CBT and in-person CBT *at post-treatment* being less than 1. Following CONSORT recommendations [24], non-inferiority analyses will be conducted both on a *per protocol* (e.g., having completed 3 weeks of treatment which is considered a dose of treatment) basis and an *intent-to-treat* basis. All other analyses will be conducted according to intent-to-treat basis, that is, by considering patient group status as randomized.

#### Missing data

We will compare the distribution of lost patients by reason between the two study groups to evaluate any differences in the reasons for losses. We will compare the rate of loss to follow-up between the two groups using the chi-square test, and if this rate is different between the two groups, interpretation of the results will be made in view of this finding. If we find any baseline variables to be associated with the loss to follow-up, then we will include these baseline variables as covariates in the models evaluating the intervention effect. In case of problematic missingness, we will use multiple imputation based on sequential regression imputation to impute missing variables. Following Rubin's method [34] for multiple imputation inference, each of the simulated complete datasets will be analyzed by standard methods, and the results will be combined to produce estimates and confidence intervals that incorporate missing-data uncertainty.

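### The plan does not commit to using recorded on-treatment pain for participants lost to follow-up, so pain-related loss that differs between arms can bias the non-inferiority contrast in either direction

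*Protocol article*

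**What the plan says.** All references are to the protocol article.

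- **Primary model (Analysis).** A linear mixed model for the survey scores: "The outcome variable in each model will be the outcome at the follow-up time points, with the baseline value of the outcome". Strata also enter as covariates. The article relies on missingness at random. Non-inferiority is read from the upper 95% confidence limit at post-treatment, against a margin of 1.
- **Loss (Missing data).** Rates and reasons of loss are compared between arms. Then: "If we find any baseline variables to be associated with the loss to follow-up, then we will include these baseline variables as covariates". Sequential-regression multiple imputation with Rubin's rules follows if missingness is thought to be a problem. No threshold and no predictors are given.
- **Daily data (Outcomes; Daily IVR calls).** "Subjects will have a maximum of 77 daily scores: 7 daily calls for the baseline assessment week and 7 daily calls". The second figure is per treatment week. Both arms are called and use the same 0–10 scale. These become weekly means and serve as a secondary outcome. Catastrophizing and skill practice are recorded in the same calls.
- **Survey timing (Outcomes).** The post-treatment survey is collected on completion of treatment or at 15 weeks, including from participants who did not complete it.

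**The concern.** Post-treatment is the first follow-up survey. A participant who returns no follow-up survey adds nothing to the primary contrast. For that participant, missing at random means at random given arm, baseline pain and strata, plus any baseline variable picked up by the search for predictors of loss.

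Pain during treatment is a natural candidate both for driving loss and for predicting the missing score. It is recorded daily until the participant stops answering, and the article itself cites reliability above 0.90 for a seven-day mean. Loss that depends on it can be at random given the trial's data, yet not at random given the planned model.

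The trial's main conclusion is at stake. If high-pain participants are lost from one arm only, that arm's mean is too low at post-treatment. In IVR-CBT this raises the chance of a false non-inferiority claim; in the in-person arm it costs power. The chi-square test compares rates of loss, so it has nothing to detect when the rates are equal and only the mechanism differs.

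**Working it through.** **1. The plan's own figure.** Inputs from Sample size calculation: "test of non-inferiority comparing IVR-CBT to CBT, with 80 % power"; "Type I error (one-sided) of 0.025, and assuming the true difference between means is 0"; "the estimated baseline NRS pain intensity score will be 7 ± 2.45 units"; "The non-inferiority margin was set at one NRS unit"; "15 % inflation for losses, the total required sample size is 230 participants (115 per group".

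n per arm = 2σ²(z₀.₉₇₅ + z₀.₈₀)²/Δ² = 2 × 2.45² × (1.960 + 0.842)²/1² = 94.2, so 95. With 15% loss, 95/0.85 = 111.8, so 112 per arm and 224 in total. The stated 230 is 6 higher (2.7%), so it is reproduced. With 115 × 0.85 = 97.75 evaluable per arm, power is 81.4%. The point below does not change the sample size.

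**2. Simulation set-up.** 115 per arm, SD 2.45, true difference 1 (exactly at the margin, so non-inferiority should be declared in 2.5% of trials). Baseline B, on-treatment mean I and post-treatment Y are trivariate normal. Assumptions not in the documents:

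- correlations: B–Y 0.5, I–Y 0.75, B–I 0.6;
- loss in IVR-CBT: logit P(loss) = a + s × (I in SD units within arm), with s = 1 or 2;
- loss in the in-person arm: at random, unless stated;
- lost participants miss every follow-up survey.

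Under the last assumption the planned contrast reduces to regression of Y on arm and B in those observed (strata were not simulated). The comparator is multiple imputation with m = 20 from arm, B and I, followed by the same regression, with total variance W + (1 + 1/m) × (between-imputation variance).

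**3. Results** (3,000 trials per row; Monte Carlo SE at 2.5% is √(0.025 × 0.975/3000) = 0.3 points).

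| Loss IVR-CBT / in-person | s | Bias, baseline only | False non-inferiority | Bias, imputation with I | False non-inferiority |
|---|---|---|---|---|---|
| 15% / 15% | 1 | −0.16 | 7.7% | −0.01 | 3.2% |
| 15% / 15% | 2 | −0.24 | 11.9% | −0.01 | 2.5% |
| 20% / 10% | 1 | −0.20 | 9.3% | 0.00 | 2.4% |
| 20% / 10% | 2 | −0.29 | 16.0% | 0.00 | 2.9% |
| 30% / 15% | 1 | −0.28 | 14.9% | 0.00 | 2.7% |
| 30% / 15% | 2 | −0.43 | 27.8% | 0.00 | 2.7% |
| 15% / 15%, same mechanism in both arms | 2 | +0.01 | 2.5% | +0.01 | 2.5% |
| 15% / 15%, random in both arms | 0 | 0.00 | 2.3% | 0.00 | 2.5% |

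**4. Sensitivity to the correlations** (15% / 15%, s = 2, 2,000 trials). With I–Y 0.6 and B–I 0.5, bias is −0.18 and false non-inferiority 8.3%. With I–Y 0.9, they are −0.31 and 16.7%.

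**5. Direction.** In a separate simulation at 15% loss per arm, with its own assumed correlations and mechanism:

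- pain-driven loss in IVR-CBT only: estimate 0.86, false non-inferiority 7.0%;
- in the in-person arm only: 1.13 and 0.5%;
- in both or neither: about 1.00 and 2%;
- imputation with on-treatment pain: about 1.00 and 2–3% throughout.

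**6. Effect of the 15-week survey.** With correlations B–Y 0.5, I–Y 0.7 and B–I 0.55, s = 1, about 20–26% dropout in IVR-CBT and 20% at random in-person, the estimate is 0.78 with 10.0% false non-inferiority if no dropout is surveyed. If half of the dropouts return the survey (an assumption), it is 0.91 with 4.6%.

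**The case against.** **The article does not stop at baseline variables.** The sentence after the quoted rule provides for multiple imputation, and its predictors could include the weekly pain means. A reader might infer that the plan excludes or ignores daily pain; the text does not support that. What stands is that the imputation is conditional on an undefined judgement, while the rule written out in full names baseline variables only.

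**An imputation predictor list is commonly left to the full protocol or SAP, which are not shown.** That is fair, and a missing list alone would be no finding. The point rests on what the article does fix: a baseline-only rule for extending the model, and an imputation that may never be run.

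**Stopping treatment is not loss of the outcome.** Dropouts are still surveyed at 15 weeks, online, on site or by post, and 6- or 9-month scores also inform the mixed model. This stands and reduces the size (step 6). It does not remove the problem, since the sample size itself allows 15% for losses.

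**The direction is assumed.** A reader might infer that the plan is biased towards non-inferiority. The documents give no loss rates or mechanisms by arm. The Background names health and mobility limitations as barriers to weekly appointments, so pain-related loss from the in-person arm is also plausible, and that would be conservative.

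**Reasons for loss are collected and compared.** This helps interpretation but does not correct the estimate.

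**The imputation was tested under favourable conditions.** On-treatment pain was fully observed and was the only driver of loss. Early leavers may have few weekly means, so the real gain would be smaller.

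**Conclusion.** The concern holds in a limited form. For participants with no follow-up survey, the stated primary model and adjustment rule use only arm, strata and baseline variables, and the plan makes no commitment to the daily pain recorded in both arms. If loss depends on on-treatment pain differently by arm, the post-treatment difference is biased: towards non-inferiority when that loss is in IVR-CBT, against it when it is in-person, and hardly at all when the mechanism is shared.

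At 15% loss per arm with pain-driven loss in IVR-CBT only, false non-inferiority is about 7–12% against a nominal 2.5%. A stronger link between on-treatment and post-treatment pain, or heavier loss, raises this; returned 15-week surveys lower it. The correlations, the loss mechanism and its confinement to one arm are assumptions, so these figures show what could happen, not what is expected. It is worth correcting because it touches the trial's main decision and the data are already being collected.

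**What to change.** In Missing data, replace the conditional wording with a fixed rule:

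- Impute missing post-treatment NRS by the sequential regression method already named, separately by arm, whatever the amount of missingness.
- Use as predictors baseline NRS, strata, the available weekly telephone pain means, and the 6- and 9-month NRS where available. Weekly skill-practice and catastrophizing means are optional.
- Fit the model in the Analysis section to each imputed set, combine by Rubin's rules, and report the non-inferiority conclusion from this analysis alongside that of the mixed model.
- Use on-treatment variables in the imputation model only. They arise after randomization, so they should not be covariates in the treatment-effect model.

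The cost is wording and some programming, with no new data and no change in sample size. Weekly means will be sparse for participants who leave early, and the change does not address loss driven by pain that was never recorded.
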